**Methodology:**

A prospective observational study is ongoing at the Benjamin Mkapa Hospital in Dodoma, Tanzania. Currently, 92 patients have been recruited into this study and process is not yet completed. The socio-demographic data, clinical correlates, and prevalence of CRAS will be determined at baseline meanwhile, the outcomes of CRAS will be determined during a follow-up period of six months from the date of enrollment. CRAS is the primary outcome of the study. Data will be categorized into CRAS and non-CRAS during statistical analysis. Mean and standard deviation will be used for normally distributed continuous variables while median and interquartile range will be used for skewed data. Frequencies and percentages will summarize categorical variables. Clinical correlates and outcomes of CRAS will be analyzed and compared by using univariate and multivariate logistic regression and Cox proportional hazards models. A two-tailed p-value of less than 0.05 will indicate statistical significance.

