### Sample size estimation

To estimate the sample size, the proportionate formula used in prospective cohort studies will be used as it has been adopted from Baraka et al., 2023 [16].

$$n={\frac{\left(Z_{\alpha }/2\sqrt{\left(\frac{r+1}{r}\right)p*\left(1-p*\right)}+Z_{\beta }\sqrt{\frac{p_{1}\left(1-p_{1}\right)}{r}p_{2}\left(1-p_{2}\right)}\right)}{{\left(p_{1}-p_{2}\right)}^{2}}}^{2}$$

$$p*=\frac{p_{2}+rp_{1}}{r+1}$$

Where by

r = ratio between the two groups

p1 = CRAS prevalence obtained from literature

p2 = expected prevalence of CRAS from the study

p1 –p2 = effect size

Zβ = standard normal variate for statistical power

Zα/2 = standard normal variate for significance level

The prevalence of CRAS in previous studies was 44.4% [2]

The prevalence of CRAS in this study is expected to be 40%

Therefore;

r = 1

p1 = 44.4%

p2 = 40%

p1 − p2 = 13%

Zβ = 0.84 for statistical power of 80%

Zα/2 = 1.96 for significance level of 95%

n = 226

Considering the 30% attrition rate adopted from previous study [2]

Therefore, the minimum sample size required to meet the objectives will be 300 patients.

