### Clinical outcomes

#### Primary outcome

Cardiorenal anemia syndrome (CRAS) is the primary outcome of this study and will be defined as a triad comprising heart failure regardless of ejection fraction, chronic kidney disease with estimated glomerular filtration rate <60mil/min/1.73m^2^ and anemia of <12 g/dl for women or <13 g/dl for men [1, 2].

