#### Secondary outcomes

Secondary outcomes will include:

**All-cause mortality** is any death that will occur within follow-up irrespective of cause [2, 11, 17–19].**Heart failure hospitalization** is defined as any admission of which the cause-specific is heart failure [2, 3, 5, 6].**Worsening renal function**: is defined when there is a change in chronic kidney disease stage to lower stage than baseline or a need of a dialysis or both [20, 21].**Worsening anemia**: is defined when there is a change of hemoglobin level to lower level from baseline which will then need either blood transfusion or erythropoietin use or both [3, 5, 22, 23].

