**Chronic kidney disease (CKD)**	Medical records/patient report	Known patient with CKD from medical records within 6 months retrospectively prior enrollment or when estimated GFR is <60mil/min/1.73m2 by CKD-EPI formula using serum creatinine level	Dichotomous, continous
**Dyslipidemia**	Medical records/patient report/blood sample	Evidence of dyslipidemia on medications from records or for unknown lipid status, when the total cholesterol ≥200 mg/dl, low-density lipoprotein cholesterol ≥130 mg/ dl, and high-density lipoprotein cholesterol < 40 mg/ dl for men or < 50 mg/ dl for women, and/or serum triglyceride level ≥150 mg/ dl	Dichotomous, categorical
**Diabetes**	Medical record/patient report/blood sample	Known patient with diabetes mellitus on medications from records or for unknown status, is when the random blood glucose is ≥11.1 mmol/L and glycosylated haemoglobin of ≥6.5%	Dichotomous, categorical
**Electrolyte imbalance**	Medical report/blood sample	Serum Na+ of <135mmol/L or >145mmol/L and/or serum K+ of < 3.5mmol/L or >5.5mmol/L	Continous
**Obesity**	Medical record/patient assessment	When the waist circumference of >94 cm for males or >88 cm for females; or calculated waist-hip ratio (WHR) of >0.9 for men or of >0.8 for women	Dichotomous, categorical

#### Objective 3

Aims to determine the outcomes of the cardiorenal anemia syndrome among the patients with heart failure within six months follow up period [2, 5, 7, 11, 25] Table 3.

**Table 3 pone.0292764.t003:** Summary and description of variables for the objective number 3.

Variable	Method of measurement	Operational definition	Level of measurement
**All-cause mortality**	Medical records or close relative through phone contact	Any death occurs within six month follow up irrespective of the cause of death	Dichotomous
**Heart failure hospitalization**	Medical record/patient report/assessment	admission of which cause-specific is heart failure	Continuous
**Worsening renal function**	Medical record/patient report/blood sample	When there is a change in Chronic kidney disease stage or a need of dialysis or both	Continuous
**Worsening anemia**	Medical record/patient assessment/blood sample	Change of hemoglobin level to lower level from baseline or a need of blood transfusion or erythropoietin use or both	Continuous

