*Lipid profile*. Dyslipidemia is defined as total serum cholesterol ≥200 mg/dL, or LDL-cholesterol ≥130 mg/dL, or serum triglyceride ≥150 mg/dL, or HDL-cholesterol <40 mg/dL for women and <50 mg/dL for men [16, 33].

*Blood sugar measurement*. Diabetes mellitus will be defined as either known patient with type 1 or 2; and for unknown diabetic status, is when random blood glucose by using blood from finger prick is ≥11.1mmol/L and glycated hemoglobin is ≥6.5% [14, 34].

*Iron studies*. Iron deficiency will be defined as serum ferritin of <100μg/l and high sensitive C-reactive protein of ≥ 3 mg/dl [35], or serum ferritin of 100 to 300 μg/l and transferittin saturation (TSAT) ≤ 20% [7, 10–12, 36].

*Full blood picture*. Anemia will be defined when hemoglobin ≤ 12g/dl for women or ≤ 13g/dl for men. Mean Corpuscular Volume (MCV) and Mean Corpuscular Hemoglobin (MCH) will be recorded to characterize the type of anemia [2, 12, 16].

*Serum electrolytes*. Electrolyte imbalance will be considered when the serum sodium is ≤ 135 mmol/l (hyponatremia) or ≥ 145mmol/l (hypernatremia) and / or potassium level of ≤ 3.5mmol (hypokalemia) or ≥ 5.3 mmol/l (hyperkalemia) [20, 33, 37].

*Blood creatinine*. Chronic kidney disease will be defined following estimation of glomerular filtration rate. Glomerular Filtration Rate will be calculated by using CKD-EPI formula by adjustment of African-American correction factor and value of <60mil/min/1.73m2 will be considered as chronic kidney disease [34, 37, 38].

*Two-dimension transthoracic echocardiogram (2D-TTE)*. Transthoracic Echocardiography (model Vivid TM T9 manufactured by GE Healthcare, USA 2018) will be used for recommended patients who are either newly diagnosed patients or for previous known HF patients of which their echocardiogram reports are of more than 6-months prior to index contact. Transthoracic Echocardiogram will be done by experienced echocardiographer and/or confirmed by consultant cardiologists. Depending on condition of the patient so, a patient will be instructed to undress and expose the chest then, the patient will lie on the left lateral decubitus position and then, change to supine position during imaging for different echocardiogram views. The imaging will take 10 to 20 minutes.

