#### Follow-up procedure

Every patient will be followed up on monthly basis within 6-months via phone calls or during regular clinic visit. In case a participant is not reachable following 3 phone calls on 3 alternative days on every fourth week of follow-up month or during clinic visit. Failure to be reachable will indicate lost to follow-up.

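### One index creatinine, even during an acute heart failure admission, can establish the chronic kidney disease part of CRAS, so transient renal dysfunction can be counted in the primary outcome

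*Protocol article*

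**What the plan says.** - **Primary outcome:** CRAS is heart failure plus anemia plus "chronic kidney disease with estimated glomerular filtration rate <60mil/min/1.73m^2". Table 1 repeats the eGFR threshold. Neither gives a duration.
- **Laboratory and imaging investigations, Blood creatinine:** an eGFR "value of <60mil/min/1.73m2 will be considered as chronic kidney disease".
- **Study variables, Table 2:** CKD is "Known patient with CKD from medical records within 6 months retrospectively prior enrollment or when estimated GFR is <60mil/min/1.73m2 by CKD-EPI formula". The two routes are joined by *or*, so the index eGFR is enough alone.
- **Inclusion criteria:** CKD may be shown by records from the six months before enrollment or, for a new patient, by the creatinine at the index contact. A separate criterion admits inpatients whose index diagnosis is acute heart failure.
- **Abstract, Methodology:** "prevalence of CRAS will be determined at baseline".
- **Follow-up procedure:** patients are "followed up on monthly basis within 6-months via phone calls or during regular clinic visit". These contacts serve the secondary outcomes. Nothing says they confirm or revise baseline CKD.
- **Study variables, Objective 2:** creatinine and echocardiography records are accessed from 18 February 2023 onwards.

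**The concern.** A single creatinine cannot separate chronic from transient renal dysfunction, and an acute heart failure admission is a setting where a temporary rise is plausible. The article names a chronic condition as its primary outcome but measures a reduced eGFR on one day.

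All three objectives use this classification. Prevalence counts it directly. The logistic models look for correlates of it. The Cox models compare CRAS with non-CRAS patients. If misclassified patients come mainly from acute admissions, part of what is reported as a CRAS association may reflect acute presentation.

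This is not detail left to an analysis plan: the article fixes the rule in several places, and each accepts one value.

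**Working it through.** No figure in the article depends on this rule, so there is nothing to reproduce. The check compares the definitions and then illustrates the possible size.

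**1. Can a transient case be counted?** Take a new inpatient with acute heart failure, no earlier creatinine, an index eGFR below 60 and hemoglobin below the threshold. The patient is eligible, has CKD under Table 2 and the Blood creatinine paragraph, and meets every part of the primary outcome. No section requires a second value, a duration, a sample after stabilisation or exclusion of acute kidney injury. The answer is yes. Patients with a low eGFR in earlier records are less exposed, and non-anemic patients are not counted as CRAS at all.

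**2. Prevalence if the CKD inclusion criterion is not mandatory.** Every share below is an assumption. Let *s* be the share of CRAS cases whose CKD rests on the index value alone and *t* the share of those that are transient. CRAS prevalence with persistent CKD = observed prevalence × (1 − *s* × *t*). For the observed value I use the article's planning figure ("The prevalence of CRAS in this study is expected to be 40" percent).

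| *s* | *t* | falsely labelled, *s* × *t* | persistent-CKD CRAS | difference (points) |
|---|---|---|---|---|
| 0.3 | 0.1 | 3% | 0.40 × 0.97 = 38.8% | 1.2 |
| 0.3 | 0.3 | 9% | 0.40 × 0.91 = 36.4% | 3.6 |
| 0.6 | 0.2 | 12% | 0.40 × 0.88 = 35.2% | 4.8 |
| 0.6 | 0.3 | 18% | 0.40 × 0.82 = 32.8% | 7.2 |

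A second parameterisation is share acute × share of those with a transient eGFR below 60 × share of those anemic. Assuming 30–50%, 10–30% and 50–60% gives 0.30 × 0.10 × 0.50 = 1.5 points to 0.50 × 0.30 × 0.60 = 9 points.

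For scale, the 95% sampling half-width at 40% and n = 300 is 1.96 × √(0.40 × 0.60 / 300) = 5.5 points.

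**3. Prevalence if the criterion is mandatory.** Every enrolled patient then has CKD by one route or the other, and transient cases enter the denominator as well as the numerator. Let *u* be the transient share of those enrolled, and *a*T and *a*P the anemia shares in transient and persistent cases. Treating all enrolled patients as having an index eGFR below 60:

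- observed prevalence = *u* × *a*T + (1 − *u*) × *a*P
- prevalence among persistent cases = *a*P
- difference = *u* × (*a*T − *a*P)

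With *u* from 0.30 × 0.10 = 0.03 to 0.50 × 0.30 = 0.15, and anemia shares of 50% and 60% either way round, the difference is at most 0.15 × 0.10 = 1.5 points, in either direction. It is zero if anemia is equally common in both.

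**4. Outcome comparison.** If a share *f* of the CRAS group is transient, the group's event risk is (1 − *f*) × *R*P + *f* × *R*T, which differs from *R*P by *f* × (*R*T − *R*P). The sign depends on whether transient cases fare worse or better than persistent ones, which the article does not say. Reclassifying those patients would also change the comparison group.

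**The case against.** The strongest reply is that the consequences are not shown. All the shares are assumed, and much of the illustrated range lies inside the 5.5-point sampling half-width. The prevalence effect also depends on whether the CKD inclusion criterion is mandatory, and the list of criteria is ambiguous because its heart failure items are plainly alternatives. All of this stands. It limits what can be said about size but does not touch the definition, which accepts one value.

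Four stronger readings may tempt a reader, and the article does not support them:

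- **That CRAS hazard ratios are biased upward.** Including patients without persistent CKD may also dilute the contrast. Confounding by acute presentation could exist even with perfect CKD ascertainment.
- **That a record of CKD without an eGFR below 60 qualifies for CRAS.** Table 2 allows it for the CKD variable, but the Primary outcome section and Table 1 both require eGFR below 60. CKD is also not among the correlates that Data analysis names for logistic regression.
- **That recovery from an acute dip will count as worsening renal function.** The Secondary outcomes section gives a direction, "change in chronic kidney disease stage to lower stage than baseline". Only Table 3 omits it, which is a separate inconsistency.
- **That follow-up creatinine can simply confirm baseline CKD.** No creatinine is scheduled, and contacts may be by phone. Confirmation from a later value also requires survival until then, so early deaths could never be confirmed. In a Cox model timed from enrollment that is immortal-time bias.

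**Conclusion.** The point holds as a flaw in the definition. The primary outcome is named as chronic, yet one index eGFR below 60 can establish it, including during an acute admission, so anemic patients with transient dysfunction can be counted as CRAS.

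Prevalence can be overstated, and acute and chronic dysfunction can be mixed in the correlate and outcome analyses. The size is unknown. The illustrations give 1.2 to 9 points if the CKD criterion is not mandatory, and at most 1.5 points in either direction if it is; all rest on assumed shares. Where bias exists, a larger sample would not reduce it. The direction for hazard ratios is uncertain. The point does not invalidate the study but should be settled before analysis.

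**What to change.** 1. Keep the single-value definition but label it *reduced eGFR at index*.
2. Classify CKD as *confirmed* at baseline only when an earlier eGFR below 60 is in the pre-enrollment records already accessed from 18 February 2023.
3. Report prevalence and hazard ratios for confirmed CRAS beside those for the single-value definition.
4. Show acute admissions and chronic entrants separately, or adjust the Cox model for acute admission.
5. Use follow-up creatinine, where available, only in a descriptive sensitivity analysis of prevalence, never to define exposure in a Cox model timed from enrollment.
6. State whether the CKD inclusion criterion applies to every patient, since the meaning of the prevalence depends on it.

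The cost is small: wording, two flags per patient (earlier low eGFR, route of entry) and extra table columns, with no new visits or tests. The downside is that patients without an earlier value stay unconfirmed, so the confirmed group is smaller and its estimates less precise.

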#### Follow-up procedure

Every patient will be followed up on monthly basis within 6-months via phone calls or during regular clinic visit. In case a participant is not reachable following 3 phone calls on 3 alternative days on every fourth week of follow-up month or during clinic visit. Failure to be reachable will indicate lost to follow-up.

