### Data analysis

All completed questionnaires will be coded before entered into dataset on Microsoft excel. SPSS windows version 25 program (IBM SPSS, Chicago IL) will be used for data management and analysis [16]. Data will be classified as CRAS or non-CRAS groups. Data will be presented as means **±** standard deviations for continuous variables with normal distribution, or median and interquartile range for no-parametric (skewed) variables [1, 2, 13]. Categorical variables will be presented as frequencies and percentages. Socio-demographic variables and clinical correlates of cardiorenal anemia syndrome at baseline will be analyzed and compared using Pearson chi-squared test for the categorical variables, and independent student’s t-test for the continuous variables [1, 2, 9]. The clinical correlates including age, gender, alcohol use, smoking history, hypertension, obesity, diabetes, and dyslipidemia and iron deficiency will be analysed and compared by using univariate and multivariate logistic regression. Cox proportional hazards model will be used to analyze and compare the outcomes of CRAS. A two-tailed p—value of less than 0.05 will indicate statistical significance [2, 7, 13].

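### Patients are classed as lost because they cannot be reached, with no prior check of the death and admission sources in Table 3, so loss can be informative for objective 3

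*Protocol article*

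**What the plan says.** - **Contact schedule** (Follow-up procedure): "Every patient will be followed up on monthly basis within 6-months via phone calls or during regular clinic visit". The section on evaluation of the participants makes these same calls and visits the means of assessing the secondary outcomes.
- **Loss rule** (Follow-up procedure): it applies to a participant "not reachable following 3 phone calls on 3 alternative days on every fourth week of follow-up month or during clinic visit", and then "Failure to be reachable will indicate lost to follow-up". The section mentions no relative, no record check, no renewed attempt in later months and no date last known alive.
- **Sources** (Study variables, Table 3): all-cause mortality comes from "Medical records or close relative through phone contact". Heart failure hospitalization comes from "Medical record/patient report/assessment", with no relative named.
- **Definition of death** (Secondary outcomes): it "is any death that will occur within follow-up irrespective of cause".
- **Analysis** (Data analysis): "Cox proportional hazards model will be used to analyze and compare the outcomes of CRAS". No censoring rule is stated.
- **Attrition** (Sample size estimation): "Considering the 30% attrition rate adopted from previous study".

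**The concern.** The loss rule turns on whether the patient can be reached. In a heart failure cohort, having died or being in hospital is an obvious reason for not answering a call or attending a clinic. If silence alone closes follow-up, the patients removed are partly those who have just had the event under study. A Cox model relies on censoring being unrelated to the outcome, given the covariates.

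Table 3 lists sources that do not need the patient to answer, but nothing links them to the moment of closure. Because only deaths within follow-up count, a patient coded lost may also be read as outside the definition.

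At stake are the estimates for objective 3: mortality, heart failure admission and the comparison of CRAS with non-CRAS. The comparison suffers if tracing or loss differs between the two groups.

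**Working it through.** **Inputs.** From the protocol: 30% attrition, 300 patients, six monthly rounds. Assumed, because the protocol does not give them: true six-month mortality M, and the share s of deaths that end up classed as lost.

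**The plan's own figure.** The only stated figure that bears on this point is the 30% allowance: 0.30 × 300 = 90 patients, leaving 210. Raising 226 by 30% gives 226 × 1.30 = 294, close to the stated 300. How 226 was reached does not affect this point.

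**How easily 30% could arise.** If one missed round were final, which the protocol does not say, the per-round chance q of being unreachable would satisfy 1 − (1 − q)^6 = 0.30. Then q = 1 − 0.70^(1/6) = 0.058, or 5.8% per round.

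**Effect on a complete-case mortality proportion.** With share lost L, observed mortality among those not lost is M(1 − s)/(1 − L). For M = 20% there are 60 deaths in 300, and with L = 30% there are 210 patients not lost:

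| Share of deaths classed as lost, s | Deaths seen / patients not lost | Observed | True |
|---|---|---|---|
| 0 | 60/210 | 28.6% | 20% |
| 0.25 | 45/210 | 21.4% | 20% |
| 0.30 | 42/210 | 20.0% | 20% |
| 0.50 | 30/210 | 14.3% | 20% |
| 0.75 | 15/210 | 7.1% | 20% |

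Observed mortality is too low only when s exceeds L, and too high when s is below L.

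**Other values of M, at L = 30%.**
- M = 9.5% (the lower mortality figure in the Introduction): 0.095/0.70 = 13.6% at s = 0, and 0.0475/0.70 = 6.8% at s = 0.5.
- M = 40% (assumed): 0.40/0.70 = 57.1% at s = 0, and 0.20/0.70 = 28.6% at s = 0.5.

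**Effect on the group comparison.** The ratio of observed proportions equals the true ratio multiplied by [(1 − s₁)/(1 − L₁)] ÷ [(1 − s₀)/(1 − L₀)], where 1 is CRAS and 0 is non-CRAS. If s and L are equal in the groups, the factor is 1. With equal L, s₁ = 0.50 and s₀ = 0.25, it is 0.50/0.75 = 0.67; with the shares swapped it is 1.50. The comparison can move either way.

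**What this does not model.** A Cox analysis keeps the time before loss. Its estimated death rate would therefore lie below the complete-case figure, and the break-even value of s would lie below L. The table shows that the result is sensitive to s and that the direction can turn. It does not predict the Cox bias.

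**The case against.** The strongest reply is that Table 3 already covers the problem. Deaths are to come from records or a relative, and admissions from the record among other sources; none of these needs the patient to answer. The Follow-up procedure does not say that tracing stops, and a patient found dead has an outcome and need not be coded lost. On this view only a cross-reference is missing, which a condensed article may leave to the full protocol. Censoring details ordinarily belong in an analysis plan that is not shown.

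Much of this stands, and it rules out several inferences a reader might draw:

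- **That mortality is understated.** This holds only if enough deaths are classed as lost. If Table 3 tracing finds every death while silent survivors drop out, mortality is overstated.
- **That one failed round closes the patient.** The text is silent on re-contact. Its monthly wording is compatible with renewed attempts, and a clinic visit is also part of the rule.
- **That 90 patients will have unknown vital status.** The 30% is a sample-size allowance taken from another study, not a forecast of what this call rule produces.
- **That the hazard ratio is attenuated by a particular amount.** Any such figure rests on assumed death and loss rates.

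The reply does not remove the defect. The loss rule is a stated operating rule, and a list of sources for a variable does not say when a patient may be closed. Late or uneven use of those sources is itself a problem: tracing deaths while dropping silent survivors is as lopsided as missing the deaths. For admissions the cover is thinner, since no relative is named and the protocol does not say whether admissions to other hospitals are captured.

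**Conclusion.** The point holds in conditional form. The Follow-up procedure and Table 3 are not reconciled, so being unreachable can close a patient before the sources named for death and admission are tried. Loss can then be informative for the Cox analysis of objective 3, and mortality and the CRAS hazard ratio can be biased.

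The protocol does not fix the direction or the size. Under 30% loss and an assumed true mortality of 20%, the complete-case range of 28.6% to 14.3% corresponds to between none and half of the deaths being classed as lost. That censoring takes place at loss is inferred from the choice of a Cox model. Objectives 1 and 2 use baseline data and are not affected. This should be corrected, but it does not undermine the study as a whole.

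**What to change.** Revise the Follow-up procedure paragraph as follows:

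1. Before coding a patient lost, call the recorded relative and check the Benjamin Mkapa Hospital record.
2. State that a missed round is not final, and keep the patient in every later monthly round.
3. At month 6, seek vital status for every patient, CRAS and non-CRAS alike, from both Table 3 sources. Ask the relative about heart failure admissions as well, and add the relative to that row of Table 3.
4. Code lost only if all of these fail, and censor at the date last known alive.

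The cost is one revised paragraph, one table entry, and a few extra calls and record look-ups by the existing team. The abstract reports 92 patients recruited with enrolment still open, so on that account the change can still be made.
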